### Adherence

Supportive strategies will be implemented to promote adherence and minimize dropout. Before enrollment, participants will be informed about study procedures and expectations. Session scheduling will be standardized while accommodating participants’ daily routines and fatigue levels. To support attendance, participants will receive appointment reminders via phone calls, emails, and/or text messages, and attendance will be monitored throughout the intervention. Missed sessions will be rescheduled within the same week whenever feasible. Participants who discontinue the intervention will be contacted and invited to complete post-intervention outcome assessments (T1) whenever feasible.

### Concomitant Care

To enable an isolated assessment of intervention effectiveness, participants will not be permitted to receive any additional physical therapy, rehabilitation, or structured exercise programs targeting the lower extremities (hip, knee, ankle, and foot) during the study. This restriction includes manual therapy, therapeutic exercises, electrotherapy, and similar lower-extremity interventions. The restriction applies only to lower-extremity physical interventions; participants may continue treatments for systemic health conditions, speech therapy, neuropsychological interventions, and routine medical follow-ups. The use of additional robotic devices or experimental treatments that could directly or indirectly affect lower-extremity function is prohibited. If an unforeseen need for additional lower-extremity treatment arises, it will be reported to the principal investigator and managed according to the study protocol.

### Criteria for Discontinuing or Modifying the Study

Participants may be withdrawn, or the assigned intervention may be discontinued or modified, in the following situations: (1) a serious adverse event or clinically significant complication (eg, cardiovascular instability, sudden neurological deterioration, syncope, medical emergency, or acute pain increase); (2) intolerable pain, muscle spasms, or excessive fatigue; or (3) unexpected clinical changes preventing continued participation. Decisions will be made by the principal investigator in consultation with the physiatrist, prioritizing participant safety and clinical status. Participants may withdraw at any time without providing a reason. Data collected up to withdrawal will be stored in encoded form in accordance with confidentiality principles.

### Harms

All AEs potentially related to the intervention, or expected in this population, will be systematically monitored and documented. AEs will be assessed through (1) active inquiry about new or worsening symptoms at the start of each session, (2) direct observation of discomfort or physical strain during sessions, and (3) participant self-report at any time (telephone, text, or email). Anticipated AEs include musculoskeletal pain, joint stiffness, skin irritation from device contact, overexertion, fatigue, emotional frustration, and transient increases in muscle tone or spasticity. AEs will be recorded by the treating physiotherapist at each session using a standardized AE log; events between sessions will be captured through participant contact and, when needed, review of relevant clinical records. Each AE will be documented (onset, duration, severity, action taken, outcome, and relatedness). Serious adverse events will be reported immediately to the principal investigator and, where required, to the ethics committee, and all AEs will be classified and reported in study publications.

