### Blinding

This study will be single blind (assessor blinded). Outcome assessments will be performed by a trained research assistant blinded to group allocation and not involved in referral, randomization, intervention delivery, or trial coordination. Due to the nature of the intervention, participants and the treating physiotherapist cannot be blinded.

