#### Robotic System

The BalanSENS robotic rehabilitation system will be used in the RTG. The system includes a fixed, platform-based end-effector ankle-foot robot featuring a parallel manipulator with a 3-degree-of-freedom rotary-prismatic-spherical configuration [38,39]. The usability of the system has been previously evaluated in healthy individuals [39].

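### The opening sentence of Harms restricts adverse event recording to possibly related or expected events, which conflicts with the later sentences and lets non-serious events that are neither go unlogged

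*Protocol article*

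**What the plan says.** The Harms section begins with a scope rule: "All AEs potentially related to the intervention, or expected in this population, will be systematically monitored and documented".

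The rest of the section is worded more broadly. Events are sought through "active inquiry about new or worsening symptoms at the start of each session", through direct observation during sessions, and through "participant self-report at any time (telephone, text, or email". On documentation it says "Each AE will be documented (onset, duration, severity, action taken, outcome, and relatedness" will be captured, so relatedness is one of the recorded fields. On publication it says "all AEs will be classified and reported in study publications". Serious events go at once to the principal investigator, with no condition on relatedness or expectedness.

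On who keeps the log: "AEs will be recorded by the treating physiotherapist at each session using a standardized AE log". The Blinding section adds that "participants and the treating physiotherapist cannot be blinded".

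Oversight and Monitoring says that adverse events are monitored throughout, without a qualifier. It also says that no independent data monitoring committee will be formed. Study Objective and Hypothesis names safety monitoring as part of the evidence for feasibility.

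**The concern.** A scope rule that depends on possible relatedness requires a judgment about cause before an event is written down. The same section treats relatedness as something assessed for each written event. If the opening sentence governs, part of that assessment has been made, unrecorded, at the point of entry.

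Two things are at stake. First, the person keeping the log knows the arm. What counts as possibly related depends on which treatment was given, so the threshold for writing an event down can differ between robot and manual training. The list of anticipated events also includes skin irritation from contact with a device, which fits the robotic arm more readily than the manual one. Second, a single event may reasonably look unrelated, yet several similar events across participants may not. That pattern can be seen only if each event was logged.

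This matters more here because safety data feed the feasibility hypothesis and no independent committee will look at them.

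**Working it through.** The plan gives no adverse event rate and no figure to reproduce, so no arithmetic applies. The check is to read the scope sentence against the other sentences and work through the cases it creates.

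**Step 1: what the scope sentence admits.** Its two conditions are joined by *or*, so an event is in scope if either holds.

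| Possibly related? | Expected? | In scope of the opening sentence? |
|---|---|---|
| Yes | Yes | Yes |
| Yes | No | Yes |
| No | Yes | Yes |
| No | No | No |

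One class of four is excluded: events that are unexpected and also not considered possibly related.

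**Step 2: remove what other routes cover.** Serious events have an unqualified reporting route in the same section. The excluded class therefore reduces to non-serious events that are unexpected and considered unrelated.

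**Step 3: compare with the later sentences.** There are two ways to read them.

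- *The later sentences inherit the scope.* The sentences on documenting each event and reporting all events then refer to events as already defined by the opening sentence. The class from step 2 need not be logged, and full reporting covers only what was logged.
- *The later sentences mean what they say.* Every event is then documented and reported, and the opening sentence contradicts them.

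The text does not settle which reading applies. The open inquiry at each session does not settle it either, because it governs how symptoms are found, while the opening sentence governs which of them are documented.

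**Step 4: check against the withdrawal rules.** Criteria for Discontinuing or Modifying the Study allows participation to end because of an unexpected clinical change. If such a change were non-serious and thought unrelated, it could end a participant's involvement and still fall outside the documentation rule in Harms.

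**Step 5: who makes the entry judgment.** The article says that the treating physiotherapist records events. It does not say who judges relatedness or expectedness. Oversight and Monitoring gives the physiatrist safety decisions about continued participation, which is a different task. That the recorder also makes the entry judgment is therefore a possibility left open, not a stated procedure.

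**The case against.** The strongest reply is that the section, read as a whole, already captures everything that matters. Events are actively sought at every session, participants can report at any time, each event is documented, and all events are published. Unexpected events that the device might have caused are explicitly in scope, and serious events are covered regardless. The relatedness field still has a purpose, because expected events enter whatever their cause. An unblinded recorder is a consequence of the design and not a mistake. The article condenses a fuller protocol that may hold the log instructions.

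Most of this stands, and it limits the point. It does not remove it: the scope sentence is stated text, not an omission that a fuller document would fill, and it either narrows the log or conflicts with what follows.

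Four stronger readings are tempting and are not supported.

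- A reader might infer that unexpected events in general are filtered out. The *or* in the rule keeps unexpected but possibly related events in.
- A reader might infer that the therapist applies the filter. The article says only that the therapist records events.
- A reader might infer that this is the first use of the device in patients, because "The usability of the system has been previously evaluated in healthy individuals". That sentence does not say there has been no earlier patient use.
- A reader might gauge the defect from the sample size. With the 19 per group in Sample Size, one event is 1/19 = 5.3 percentage points, and zero events in 19 gives a one-sided 95% upper bound of 1 − 0.05^(1/19) = 14.6%. Both figures would be the same with perfect recording, so they do not measure what the rule loses.

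**Conclusion.** The point holds in a narrow form. The opening sentence of Harms is inconsistent with the later sentences of the same section. Read literally, it allows non-serious events that are both unexpected and considered unrelated to go unlogged in either arm. Because the log is kept by someone who knows the arm, a relatedness judgment at entry could differ between arms, and a cross-participant pattern in such events could not be recovered.

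The size cannot be put as a number. The article gives no event rate and no basis for how many events fall in the excluded class. The Statistical Analysis section describes no between-arm test of adverse events, so the consequence is for the descriptive safety comparison and the feasibility conclusion, not for the primary analysis.

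The conclusion assumes that staff could follow the opening sentence as written. If the log instructions already require every event to be entered, only the wording of the article needs correcting. The change is worth making either way.

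**What to change.** Delete the qualifier from the opening sentence of Harms. State instead that every new or worsening event in either arm is recorded regardless of relatedness or expectedness, that relatedness is assessed after recording, and that all events are reported by arm. Bring the log instructions into line if they repeat the qualifier. Stating who assesses relatedness would help, although that may already be in the full protocol.

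The cost is one sentence and a slightly longer log. No outcome, sample size or analysis changes. The article reports four participants enrolled as of March 25, 2026, so on that date the change would have affected few records. Events never logged may not be recoverable later.

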### Ethical Considerations

#### Research Ethics Approval

The initial study protocol, informed consent forms, and study-related documents were approved by the Istanbul Medipol University Clinical Research Ethics Committee (approval E-66291034‐202.3.02-8175) on December 4, 2025. The current approved protocol is version 4, dated January 2026, and was approved by the same ethics committee on January 14, 2026. Written informed consent will be obtained from all participants before enrollment. The consent process will be conducted by physiotherapists trained in research ethics and legal requirements; participants will have the opportunity to ask questions before signing. The study is registered at ClinicalTrials.gov (identifier: NCT07091045). Study findings will be disseminated through peer-reviewed publications and scientific conference presentations.

#### Protocol Amendments

Any protocol modifications that may affect participant safety, burden, or expected benefits will be submitted to the ethics committee for approval prior to implementation. Participants will be informed of relevant changes, and reconsent will be obtained when necessary. All amendments will be documented using updated protocol version numbers and dates and reported in accordance with applicable regulatory requirements.

#### Confidentiality and Access to Data

Access to identifiable medical records will be restricted to authorized personnel at Istanbul Medipol University and Medipol Health Group Hospitals when required for study verification and regulatory compliance. All personnel with access to such records will be bound by professional confidentiality obligations. Participant data will be handled in accordance with applicable data protection legislation (including the Personal Data Protection Law) and relevant ethical standards. Study data will be coded, and identifying information will be stored separately from research datasets. Data collection will be limited to the clinical assessments and outcome measures defined in the protocol. Analyses will be conducted on deidentified datasets. Data will be used solely for the purposes of this research. No identifiable participant data will be shared publicly.

#### Dissemination Policy

Study results will be disseminated regardless of direction or statistical significance via international peer-reviewed publications, presentations at neurological rehabilitation conferences, and inclusion in a PhD dissertation. Individual participant data will be presented only in anonymized form using study codes. A summary of overall study findings may be provided to participants upon request in a clear, nontechnical format. Data analysis and reporting will be completed following study completion and disseminated through appropriate scientific channels. Any educational materials or professional training outputs developed from the findings will be based on aggregated, anonymized results.

## Results

This study is supported by the Scientific and Technological Research Council of Turkey (TÜBİTAK) under the 1002-A Rapid Support Program (grant 225S390). The study protocol was conditionally approved for funding on August 22, 2025, and final funding approval was granted following revisions on January 16, 2026. Recruitment began in March 2026 and is planned to continue until May 2027. As of March 25, 2026, four participants have been enrolled and are currently receiving the assigned intervention. Data analysis will begin once all enrolled participants have completed post-intervention assessments.

## Discussion

This study protocol describes an assessor-blinded, parallel-group randomized controlled trial designed to evaluate the effectiveness of a structured robot-assisted ankle-foot sensorimotor training program compared with a content-matched manual training program in individuals with chronic stroke. The proposed intervention addresses persistent lower-extremity motor and somatosensory impairments after stroke by integrating passive ROM or stretching, plantar vibrotactile localization training, VR-based proprioceptive training, and active or active-assisted ankle ROM training within a single standardized program. By targeting both sensory and motor components of ankle-foot dysfunction, this trial aims to provide clinically relevant evidence for a distal, ankle-foot–focused robotic rehabilitation approach.

A key rationale for the present protocol is that post-stroke gait and balance impairments are not solely motor problems but also reflect altered somatosensory input, impaired proprioception, abnormal muscle tone, weakness, and reduced motor control [7,10,55,56]. The plantar surface and ankle provide important sensory information for postural orientation, weight transfer, and rapid postural corrections [7,27,49]. Therefore, rehabilitation strategies that address ankle mobility and motor control together with plantar tactile and proprioceptive processing may be particularly relevant for improving functional walking and balance [10,49,50]. In this context, the BalanSENS protocol differs from many previous ankle robotic interventions by embedding plantar vibrotactile localization and proprioceptive training into the same robot-assisted rehabilitation framework rather than applying sensory stimulation as an isolated modality.

Another important feature of the protocol is the structured integration of passive and active training components. Passive ROM and stretching are commonly used to maintain or improve ankle mobility and reduce resistance to movement, but passive repetition alone may be insufficient to optimize motor learning [21,58]. Therefore, the proposed program progresses from passive and sensory-focused elements toward active, performance-based ankle training. During active ROM training, VR-based tasks and real-time performance-sensitive adaptation are used to promote active engagement and individualized task difficulty. The assist-as-needed strategy is expected to support participation by providing assistance when required while encouraging voluntary motor output. This approach is consistent with contemporary motor learning principles emphasizing task specificity, sufficient repetition, active engagement, feedback, and individualized progression [58].

A further strength of this trial is the use of a manual training group that is designed to be content matched to the robotic intervention. Many studies compare robotic rehabilitation with usual care or broadly defined conventional therapy, which may make it difficult to interpret whether observed effects are related to robotic delivery itself or to differences in dose, structure, attention, or task content [35,40]. This design may provide a more direct evaluation of the added value of robot-assisted delivery, including standardized trajectory control, VR-based feedback, real-time adaptation, and sensor-supported safety monitoring.

In this study, training dose, session structure, progression rules, ROM safety limits, and feedback conditions are predefined. The use of a standardized robot-assisted protocol may also help address the heterogeneity reported in previous ankle rehabilitation studies. In the robot-assisted group, session-specific calibration will allow training parameters to be individualized while maintaining standardized safety boundaries. This balance between standardization and individualization may improve both reproducibility and clinical applicability. In summary, the findings of this trial may contribute to the development of more standardized, individualized, and sensorimotor-oriented rehabilitation protocols for improving gait and balance after stroke.

## Data Availability

Data used in this study may be obtained from the corresponding author upon reasonable request.
